### Sample size calculation

Considering a clinically relevant effect of 20% change of albumin excretion rate (AER), which is half the effect of angiotensin-converting enzyme inhibitors (ACEis) on AER [24, 25], we estimated that the average AER of 100 decreased to 80 μg/min albumin (standard deviation 40) in the intervention group compared with no expected change in the placebo group. With a two-sided alpha set at 0.05 and power at 0.80 and a correlation of 0.70 between the three repeated measures, we calculated that at least 48 patients in each study group (i.e. 96 in total) would be required [26].

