##### Study procedure

At baseline, 6 weeks, and 3 months, 24-h urine will be collected for AER measurements. Information about demographic variables, lifestyle, adverse effects, compliance, and food intake will be collected by using standard questionnaires. The urine collection procedure starts in the morning and lasts 24 h; it stops at the same time point it started the day before. During collection, all of the produced urine is collected in a container that was handed out to the patient at the outpatient clinic. Within a couple of hours after the collection, urine is delivered in the outpatient clinic. AER is measured the same day as soon as possible after delivery. The patient is instructed to keep the container with urine in a dark and cool place at room temperature until delivery. At baseline and after 3 months, blood samples will be collected for determination of ADMA, sVCAM-1, sICAM-1, IL-6, and vWF and for measuring HbA_1c_ fasting glucose, lipids, creatinine, and estimated glomerular filtration rate (eGFR). Non-fasted venous blood is collected in EDTA tubes at a random moment of the day at the outpatient clinic. Plasma samples will be stored at −80 °C until analysis. Although patients are not required to fast before blood collection, we do keep a record of whether they fasted or not. In addition, body weight, blood pressure, and waist/hip circumference will be measured. In Fig. 2, we show a schedule of the study procedures. All participants receive usual care as provided by their diabetes team and must continue all of their prescribed medication, including adjustments when required. Since this may potentially affect our outcome measures, all used medications, dosage modifications, and other medical interventions during the trial will be recorded to adjust for this potentially confounding effect. We will ask the participants to keep their current lifestyle unchanged. There are no dietary restrictions during the study, except for the use of specific dietary supplement products containing at least 25 mg MOF. To control for dietary flavanols in regular food, we will use detailed dietary questionnaires to calculate the amounts.

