## Discussion

The presence of microalbuminuria is associated with endothelial dysfunction and poor cardiovascular outcome in T2D [31]. Although microalbuminuria is associated with a number of other risk factors, it is considered an independent risk factor for CVD and cardiovascular events in diabetes [31]. The exact mechanism leading from microalbuminuria to end organ damage is not yet completely understood. Endothelial dysfunction, however, might play a crucial role in this process [32]. Hypothetically, microalbuminuria is a signal of endothelial dysfunction leading to increased permeability of atherogenic lipoprotein particles [31]. In addition to endothelial dysfunction, a number of metabolic disorders are associated with microalbuminuria leading to cardiovascular damage: transvascular leaking of albumin in vessels, elevated glomerular filtration rate, elevated blood pressure, hyperinsulinemia, elevated plasma fibrinogen levels, and altered blood lipid levels and function may also play important roles [31, 32].

Treating microalbuminuria by improving endothelial function is most probably beneficial in patients with T2D. Although ACEis and angiotensin receptor inhibitors (angiotensin receptor blockers, or ARBs) are effective treatments to achieve this goal [31, 32], use of MOF as part of the dietary management may also be an effective auxiliary strategy. The individual responses to ACEis and ARBs show large variation. They are not equally effective in treating microalbuminuria in each individual patient [32]. Besides, a remarkable percentage of treated patients with T2D will eventually develop diabetic kidney disease during the course of the disease [33]. Therefore, if MOF are proven to fulfill the specific nutrient requirement, they may become a dietary tool to manage albumin excretion in patients with T2D and microalbuminuria in general and in the insufficient responders to ACEis and ARBs in particular.

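### ACE-inhibitor/ARB treatment started or changed shortly before baseline is neither screened out nor captured as described; the cost is precision and power, not bias

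*Protocol article*

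**What the plan says.** All places are in the protocol article.

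- **Inclusion criteria and Exclusion criteria.** The qualifying microalbuminuria result may be up to 6 months old. The only look-back on exposure is 4 weeks, for supplements supplying 25 mg/day or more of MOF. Nothing concerns recent starts or changes of ACE inhibitors, ARBs or other drugs that lower AER.
- **Sample size calculation.** The target is that "the average AER of 100 decreased to 80" μg/min, a 20% change, "which is half the effect of angiotensin-converting enzyme inhibitors (ACEis) on AER". This is set against the control arm: "compared with no expected change in the placebo group". The result is that "at least 48 patients in each study group (i.e. 96 in total) would be required".
- **Study procedure.** Participants "must continue all of their prescribed medication, including adjustments when required". The section accepts that this may affect the outcomes. It says that medications, dose modifications and other interventions during the trial are recorded so that they can be adjusted for.
- **Statistical analysis.** The listed fixed effects are treatment group, time, log time and treatment-time interactions. No medication term is named.
- **Discussion.** Of ACE inhibitors and ARBs, it says they "are effective treatments to achieve this goal", the goal being to treat microalbuminuria by improving endothelial function.

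**The concern.** On the protocol's own figures, a background drug can move AER by about 40 μg/min when the trial is looking for 20 μg/min. A microalbuminuria result in the preceding 6 months is the kind of finding that may prompt such treatment. Recruitment takes place through routine clinic appointments, where treatment may be reviewed. A patient whose drug was started or changed shortly before the baseline urine is eligible, and any later fall counts towards that patient's AER evolution.

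The recording clause does not reach this case. It would show that the patient takes the drug and would show changes after entry, but the text does not mention start or change dates before baseline. The protocol therefore provides for adjustment on medication changes made after randomisation, which may themselves respond to the outcome, and not on the one piece of medication history that is fixed before randomisation. What is at stake is how precisely the primary comparison is estimated.

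**Working it through.** **Inputs from the sample size section:** difference 20 μg/min, SD 40, "With a two-sided alpha set at 0.05 and power at 0.80 and a correlation of 0.70 between the three repeated measures", 48 per arm. ACE-inhibitor effect = 2 × 20% = 40%, or 40 μg/min from a mean of 100.

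**Assumptions, not in the documents:** a share f of recent starters (10%, 20% or 30%), the same in expectation in both arms, and the part of the 40 μg/min fall that comes after baseline (all or half).

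**The plan's own figure.** Two-means formula: 2 × (1.960 + 0.842)² × 40² / 20² = 62.8 per arm. Multiplying by the variance factor for the mean of three measures, (1 + 2 × 0.70)/3 = 0.80, gives 50.2, so 51 per arm. That is the closest repeated-measures variant to 48, and its power at 48 per arm is 78.2%. Since 48 is not reproduced exactly, I calibrate to the stated 80%. The implied effective SD is 20 / [2.802 × √(2/48)] = 34.97, variance about 1,223.

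**Bias.** An extra fall of 40 in a share f of each arm lowers both arm means by 40f. The expected between-arm difference is unchanged. In a simulation of 48 per arm, 40,000 trials per setting and f from 0 to 30%, the mean estimate stayed at about −20.0 for a true −20 and about 0 for a true 0, with rejection under the null of 4.8% to 5.1%.

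**Added variance and power.** Added variance = f(1 − f) × fall². Power = Φ(20 / √[2 × (1,223 + added)/48] − 1.96).

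| f | Added, full fall (40) | Power | Added, half fall (20) | Power |
|---|---|---|---|---|
| 0% | 0 | 80.0% | 0 | 80.0% |
| 10% | 144 | 75.5% | 36 | 78.9% |
| 20% | 256 | 72.2% | 64 | 78.0% |
| 30% | 336 | 69.9% | 84 | 77.3% |

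At f = 5% with the full fall, power is 77.6%.

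**Chance imbalance.** SD of its contribution to the treatment difference = 40 × √[2f(1 − f)/48] = 2.4, 3.3 and 3.7 μg/min for f = 10%, 20% and 30%, in either direction.

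**Sensitivity to the starting variance.** For a pure change score, variance is 2 × (1 − 0.70) × 40² = 960. Power at 48 per arm then starts at 88.5% and becomes 83.9%, 80.2% and 77.7% with the full fall.

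**Sensitivity to how MOF acts.** If MOF lowers AER proportionally, the absolute effect shrinks to 20 × (1 − 0.4f) = 19.2, 18.4 and 17.6 μg/min. Calibrated power with the full fall is then 72.0%, 64.9% and 58.8%.

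**The case against.** A reader might infer that recent starters mask the MOF effect, or that the trial fails because the control arm will not stay flat. The documents do not support either reading. Allocation is 1:1 and double-blind (Randomization and blinding), and the primary endpoint is the between-arm difference in AER evolution (Primary outcome measure). A drug started before randomisation is expected equally in both arms, and a fall common to both leaves the 20 μg/min contrast intact. This objection stands in full against any claim of bias.

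The size is also open to challenge. Nothing in the documents says how many patients are newly treated. The 6-month limit is explained by the variability of microalbuminuria, not by new diagnosis. Patients have at least 2 weeks to decide after being informed, so a drug started at the routine appointment would usually precede baseline by at least that long, and part of the fall may already have happened. With half the fall left, the loss is 1 to 3 percentage points. On the change-score variance, power stays at or above 80% up to about 20% recent starters. These points stand and make the full-fall figures an upper scenario.

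Finally, Study procedure recognises confounding by medication and intends to adjust for it, with details that may sit in a fuller document. That intention deserves credit. As worded, however, it concerns what happens during the trial and so leaves the pre-baseline period open. Including patients under usual care is a reasonable design choice, and this point does not contest it.

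**Conclusion.** The gap is real and its consequence is limited. Treatment started or changed before baseline, with an effect about twice the target on the protocol's own statement, is neither excluded by the listed criteria nor covered by the recording clause. The treatment difference remains unbiased. The cost is a chance-imbalance SD of about 2.4 to 3.7 μg/min against a 20 μg/min target and, from a calibrated 80%, a loss of roughly 4 to 10 points of power for 10% to 30% recent starters with the full fall, or about 1 to 3 points with half of it. Proportional action of MOF would make the loss larger; the change-score variance would leave more in reserve. All of this rests on an assumed share and time course that the documents do not give. It is a cheap improvement in precision, not a threat to validity.

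**What to change.** Before unblinding, and preferably before the planned blind review of the primary outcome, define a window before the baseline urine. For every randomised patient, extract from the medical records whether ACE-inhibitor/ARB treatment was started or changed in that window (yes/no). The investigators should set and justify its length, because the documents offer no basis for one. Add the indicator and its interaction with time to the primary mixed model as baseline terms, instead of relying on adjustment for medication changes made after randomisation.

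To the extent that recent starters fall by a similar amount, these terms remove the added variance f(1 − f) × fall² and bring power back towards the planned level. They do not undo the dilution that arises if MOF acts proportionally.

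A new eligibility rule is not needed. With protocol version 3.1 dated June 2018 and recruitment estimated to end in December 2018, it would reach only the last entrants and split the population. The indicator can be applied to everyone.

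Cost: some extraction from records the study coordinator already screens, and two model degrees of freedom (indicator and interaction with time). Usual care is untouched.

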In a prospective cohort study (European Prospective Investigation into Cancer and Nutrition, or EPIC), a significant inverse trend was observed between MOF intake and risk of T2D [13]. Another trial showed a significant association between the intake of polyphenols, of which MOF are a subclass, and a decreased risk of cardiovascular disease (CVD) [14]. Higher intakes of anthocyanins (red pigments of which condensed flavanols are the precursors) and flavones (a class of flavonoids) have been associated with significant improvements in insulin sensitivity and high-sensitivity C-reactive protein (hs-CRP) levels [15]. Grape seed extracts containing relevant concentrations of MOF significantly decreased systolic blood pressure and CRP level in patients with T2D [16]. A daily supplementation of 150 mg of MOF significantly reduced several microvascular abnormalities in patients with diabetic nephropathy and retinopathy [17, 18]. In a recent study, use of 200 mg MOF per day for 8 weeks resulted in vascular health benefits in “healthy” male smokers [19]. In the same study, MOF modulated the expression of genes associated with cardiovascular disease pathways, mainly genes involved in chemotaxis, cell adhesion, cell infiltration, and cytoskeleton organization, suggesting diminished immune cell adhesion to endothelial cells [20]. Whether MOF have a physiological effect on the renal endothelial health of patients with T2D has not yet been established.

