## Methods/design

### Study design

This study is a double-blind, randomized, controlled, multicenter trial. After giving written informed consent, eligible participants will be randomly assigned to placebo or intervention for 3 months. Outcome parameters will be measured at baseline, at 6 weeks, and at 3 months. In Fig. 1, we show the flow chart of this study. The SPIRIT (Standard Protocol Items: Recommendations for Interventional Trials) checklist for study protocols is provided as an Additional file 1.

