##### Statistical analysis

All analyses will be conducted in accordance with the intention-to-treat principle. We will use the mean (in case of normal distribution) and median values (in case of non-normal distribution) as measures of central tendency for numerical data and the standard deviation and interquartile range as measures of variability, respectively. Mixed modeling will be applied for longitudinal analyses of the data. Mixed modeling can efficiently handle data with missing and unbalanced time points. Three levels in the models will be postulated. The participating centers constitute the upper level, the patients the middle level, and their repeated measures the lower level. First, for each outcome variable, a model will be postulated, and the primary or secondary outcomes will be dependent variables. The models will include treatment group, time, and logarithm of time and treatment-time interactions as fixed effects. The deviance statistic [29] using restricted maximum likelihood [30] will be applied to determine whether the covariance structure should also include slope and intercept-slope interaction next to the intercept. No interim analysis will be performed. Analyses will be carried out by using SPSS version 21.0 (IBM, Armonk, NY, USA) (http://www-01.ibm.com/support/docview.wss?uid=swg21608060).

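### The protocol announces adjustment for medication changes during the trial as confounding, which conflicts with its intention-to-treat analysis and medication-free model; primary adjustment should be limited to pre-randomisation variables

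*Protocol article*

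**What the plan says.** Two sections of the protocol article bear on this.

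**Study procedure.** Participants receive usual care and "must continue all of their prescribed medication, including adjustments when required". Because this could affect the outcomes, "all used medications, dosage modifications, and other medical interventions during the trial will be recorded to adjust for this potentially confounding effect". On diet, the section says: "To control for dietary flavanols in regular food, we will use detailed dietary questionnaires to calculate the amounts". It names no model and no time point for either adjustment, and does not say whether they belong to the primary comparison.

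**Statistical analysis.** "All analyses will be conducted in accordance with the intention-to-treat principle". The model is then described: "The models will include treatment group, time, and logarithm of time and treatment-time interactions as fixed effects". No medication or diet term is listed. The description opens with "First, for each outcome variable, a model will be postulated", but no second model follows.

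The Background (Monomeric and oligomeric flavanols and their physiological effect) also matters. It cites a study in which grape seed extracts "significantly decreased systolic blood pressure and CRP level in patients with T2D".

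**The concern.** Allocation is random, so a change of medication made afterwards cannot be a common cause of allocation and outcome. It can be a consequence of allocation, of the patient's AER or blood pressure during follow-up, or of both. The protocol supplies the ingredients: medication is changed when the patient's condition calls for it, such changes are expected to affect the outcomes, and a blood-pressure effect of grape seed extract is cited. Blinding does not remove this path, because a blinded physician still reacts to measured values.

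Conditioning on such a variable has two effects. It removes any part of the treatment effect that runs through medication, so the target is no longer the effect of assignment. It also compares patients who are alike in medication change but may differ in the course that led to it, which can bias the estimate for either target.

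The practical risk is that two analysts, each citing the protocol, could report different treatment effects.

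**Working it through.** **Inputs from the protocol (Sample size calculation).** AER falls from 100 to 80 µg/min on the flavanol product (MOF) and does not change on placebo, so the planned difference is 100 − 80 = 20 µg/min. SD is 40 and the correlation between measures is 0.70. The protocol states no figure for the effect of adjustment, so there is none to reproduce.

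**Inputs assumed.** Rate of medication step-up, the drug's effect on AER, and the spread of within-trial worsening. The documents give none of these.

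**Model (large simulation).** With g = 1 for MOF and m = 1 for a step-up:

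- Baseline AER = 100 + b + e0
- Month-3 AER = 100 + b + w + d·g + k·m + e3
- Var(b) = 0.70 × 40² = 1120; Var(e) = 0.30 × 40² = 480; SD(w) = 20
- d is the direct effect of MOF, k the drug effect, w the worsening during the trial

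Step-up rules:

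- A: logit P(m = 1) = −1.2 + 1.5·w/20 − 1.0·g
- B: logit P(m = 1) = −1.2 + 1.5·(w + d·g)/20, so step-up follows the AER course

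Month-3 AER is regressed on g and baseline AER, without m (unadjusted) and with m (adjusted).

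| Rule | Step-up, placebo / MOF | d | k | Unadjusted | Adjusted | Difference |
|---|---|---|---|---|---|---|
| A | 30% / 17% | 0 | −20 | +2.7 | +3.0 | +0.3 |
| A | 30% / 17% | 0 | 0 | 0.0 | +2.9 | +2.9 |
| B | 30% / 12% | −20 | 0 | −20.0 | −16.0 | +4.0 |
| B | 30% / 12% | −20 | −40 | −12.8 | −16.0 | −3.2 |

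**Hand check of the unadjusted column.** The effect of assignment is d + k·(p_MOF − p_placebo). Row 1: 0 − 20 × (0.17 − 0.30) = +2.6. Row 4: −20 − 40 × (0.12 − 0.30) = −12.8. The unadjusted estimate therefore recovers the effect of assignment.

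**Reading the adjusted column.** In row 1 it does not recover the direct effect of zero, and the drug's own coefficient comes out at about +2 although the truth is −20: patients stepped up are those who were getting worse. In row 3 the direct effect and the effect of assignment are both −20, and the adjusted estimate misses both by 4, a fifth of the planned difference. In row 4 it lies between the two and equals neither.

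**A milder set of assumptions.** If step-up depends on the 6-week AER, with rates of about 15% to 23%, a drug effect of 0 to −40 and d = −20, the two estimates differ by 0 to about 1.4 µg/min (largest: −18.1 unadjusted, −19.5 adjusted). Where step-up was unrelated to both AER and arm, both estimates were −20.0.

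**Limit of the range.** These are scenarios, not a bound. If step-up differed by arm but was unrelated to the AER course, the adjusted estimate would equal d, and the gap would be k·(p_MOF − p_placebo): with k = −40 and rates of 30% and 17%, 40 × 0.13 = 5.2 µg/min. That gap would be a change of question rather than bias in the direct effect.

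**The case against.** A reader might infer that the plan puts on-trial medication into the primary model and so replaces the intention-to-treat effect. The documents do not support that. The only model specified contains no such term, and the adjustment sentence is a rationale for data collection under Study procedure. The word opening the model description leaves room for an unadjusted model followed by an adjusted one, and an analysis plan that is not shown may settle which is primary. Intention to treat in its narrow sense, everyone analysed as allocated, could also be kept in an adjusted model. All of this stands, and it limits the point to a conflict between two sections. It does not remove the point, because the protocol states adjustment as the purpose and gives confounding as the reason, and that reason is wrong for changes after randomisation.

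A reader might also infer that the diet sentence commits the same error. It does not say so. The text gives no time point, outcomes are measured at baseline as well as later ("Outcome parameters will be measured at baseline, at 6 weeks, and at 3 months"), and participants are asked to keep their lifestyle unchanged. Adjusting for intake measured before randomisation is legitimate. Likewise, medication in use at baseline is a proper covariate; the difficulty is with changes during the trial.

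Finally, nothing in the documents shows that step-up will differ by arm within three months of blinded treatment. In the first scenario above, adjustment moves the estimate by only 0.3 µg/min, or 0.3/20 = 1.5% of the planned difference. This also stands: bias is possible, not established.

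**Conclusion.** The concern holds as a conflict between sections combined with a wrong premise. Study procedure announces adjustment for medication changes during the trial as confounding; Statistical analysis specifies intention to treat and a model without a medication term. Adjusting for such changes alters the estimand and can bias the estimate.

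The size cannot be derived from the documents. Under the assumptions tabulated, the two estimates differ by 0 to about 4 µg/min, in either direction, against 20 planned. The difference is nil when medication change is unrelated to both AER and arm. Confidence is high for the conflict and the premise, and low for any particular amount of bias. On diet, the wording is ambiguous and nothing more.

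**What to change.** Reconcile Study procedure with Statistical analysis:

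- State that the primary intention-to-treat analysis uses all AER values regardless of medication changes and adjusts only for variables measured before randomisation, for example baseline use of ACE inhibitors or angiotensin receptor blockers, or baseline dietary flavanols.
- Replace the confounding rationale: medication and dosage changes during the trial are recorded so that they can be tabulated by arm.
- Label any analysis that conditions on on-trial medication as supplementary, and say what effect it is meant to estimate.
- State that any control for dietary flavanols in the primary analysis uses baseline intake only.

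The cost is the rewording of two sentences and a short addition to the analysis section. No new data collection is needed for the medication tabulation, and the stated sample size of 48 per group is unaffected. The change should be made before unblinding.
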